#### Inclusion criteria

Men ≥ 40 years.Ability to understand and the willingness to sign an informed consent.Diagnosis of LUTS secondary to BPH refractory to/contraindicated for medical treatment or patient preference for TUMT/PAE.Severe urinary symptoms on IPSS (IPSS ≥ 20), an indwelling catheter, or intermittent catheterisation. In the last two cases, the baseline IPSS is set to 35 points.A maximum flow rate (Qmax) ≤ 15 mL/s.Prostate volume at minimum 50 mL measured by transrectal ultrasound measurement (TRUS) or MRI.

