The secondary outcomes include the following:The mean IPSS of the two arms at all other follow-up occasions than the primary outcome.The mean procedure time for the conduction of TUMT and PAE as well as the calculated necrosis.Health-related quality of life measured by the mean IPSS-QoL, BII, and EQ-5D-5L. IPSS-QoL assesses the quality of life associated with symptoms from urinary problems. The BII is a self-reported, validated, disease-specific instrument for quantifying the interference of LUTS on the patient’s mental health and activity. As a measure of QoL, it is used to determine treatment outcomes in men with symptomatic benign prostatic hyperplasia [22]. The EQ-5D is the most widely applied instrument for health-economic assessment worldwide. Its index values are used in the estimation of quality-adjusted life year gains in economic evaluations of healthcare interventions [23].Mean satisfaction with treatment by a five-level bipolar Likert scale.Erectile function measured by the mean IIEF-EF score. The IIEF-EF domain score is a PROM used to measure erectile performance and assess disease severity in efficacy trials. It distinguishes between men with and without erectile dysfunction (ED), classifies levels of ED severity, and has the requisites to detect treatment-related changes in patients with ED [24, 25].Ejaculatory function measured by the mean DAN-PSS-1-sex. The DAN-PSS-1-sex is a validated instrument to determine erectile and ejaculatory function and its impact on the well-being of the patient [26].Incontinence measured by the mean ICIQ-UI-SF. The ICIQ-UI-SF is validated for evaluation of the frequency, severity, and impact on QoL of urinary incontinence [27].Mean prostate volume (PV) measured by TRUS in mL.Mean uroflowmetry outcomes of the two arms. We will be looking at voided volume, Qmax, and residual urine. Uroflowmetry is a non-invasive procedure used to measure the flow of urine throughout micturition. It provides useful information about the total voiding function and is used for diagnosis of lower urinary tract dysfunctions and evaluation of treatment response. Qmax is the value of the highest flow rate measured during the test; it will be set to zero if the patient has an indwelling catheter. Transabdominal ultrasound will be used to assess post-voided residual urine as it is accurate and non-invasive [28].Post-procedure catheterisation events, including the placement of an indwelling urinary catheter and the use of intermittent catheterisation. Catheterisation will be expressed as the reason for placement, duration, and frequency (in case of intermittent catheterisation). If an indwelling catheter is placed after the procedure, the post-procedure duration of catheterisation will be defined as days from the procedure till indwelling catheter cessation. Catheterisation for any other reason during the follow-up period will also be evaluated.Prostate-specific antigen (PSA) and creatinine. The absolute value of serum PSA (ng/mL) has a good predictive value for the determination of prostate volume. Continued PSA measurements assist in the detection of any de novo prostate cancer or progression of patients in active surveillance or watchful waiting. A rise in serum creatinine can be a result of BPH with urinary retention. Serum creatinine aids in the identification of any affection of the kidney from the procedures.De novo use of pharmacological LUTS treatment and surgical re-treatment rates will be collected from the patient’s health record.Incidence at 3 months post-procedure of urinary tract infection, acute urinary retention, dysuria, haematuria, post-embolisation syndrome (PES), hospital admission, and hospitalisation time. PES is defined as occurring within 48 h after surgery and consisting of influenza-like symptoms, pelvic pain, nausea, dysuria, or transient worsening of LUTS. Data on AEs and side effects will be collected from the patient’s health record and the follow-up visit at 3 months. Surgical complications will be categorised following the Clavien-Dindo grading [29].

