**Procedures**								
CTA	**X**							
TRUS/MRI (prostate volume)	**X**			**X**	**X**	**X**	**X**	
Blood test (PSA + creatinine)	**X**			**X**	**X**	**X**	**X**	
Uroflowmetry (flow + residual urine)	**X**			**X**	**X**	**X**	**X**	

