### Methods for additional analyses (e.g. subgroup analyses) {20b}

To address disparities between study groups, we plan to perform additional adjusted analyses correcting for baseline prostate size, age, and Qmax. No additional subgroup analysis is planned at the initiation of this trial.

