### Methods in analysis to handle protocol non-adherence and any statistical methods to handle missing data {20c}

The study is analysed as intention-to-treat. As data is expected to be missing completely at random, missing data will be handled by pairwise deletion.

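### The catheter rule for uroflowmetry covers one of three outcomes and one of two catheter types; pairwise deletion then drops men because treatment failed

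*Protocol article*

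**What the plan says.** Outcomes {12} lists the uroflowmetry measures: "We will be looking at voided volume, Qmax, and residual urine". They are compared as arm means. One catheter convention is given, for Qmax: "it will be set to zero if the patient has an indwelling catheter". For residual urine the section gives only the method: "Transabdominal ultrasound will be used to assess post-voided residual urine as it is accurate and non-invasive". It states no convention for residual urine or voided volume in a catheterised man, and none for Qmax in a man on intermittent catheterisation.

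Both catheter types are expected. The inclusion criteria admit men with "an indwelling catheter, or intermittent catheterisation. In the last two cases, the baseline IPSS is set to 35 points", so the two types are treated alike for baseline IPSS. The catheterisation item in Outcomes {12} also foresees both types after the procedure.

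Table 1 schedules uroflowmetry, flow and residual urine, at screening and at 3, 6, 12 and 24 months, with no exception for catheterised men. Section {20b} plans "additional adjusted analyses correcting for baseline prostate size, age, and Qmax". Section {20c} assumes data missing completely at random, and "missing data will be handled by pairwise deletion".

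**The concern.** A man who needs a catheter at a follow-up visit is a poor outcome for bladder emptying. The zero rule recognises this for Qmax with an indwelling catheter. For the other two measures, and for intermittent catheterisation without voiding, nothing takes its place, and the general rule on missing data applies. That rule removes the man as if his value had been lost by chance, when it is absent because he could not void. If one arm leaves more men in that state, its flow and volume means are computed on a more favourable remainder. The three uroflowmetry comparisons may then describe different sets of men at the same visit.

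**Working it through.** The documents give no figure on this point to reproduce, and the sample size concerns the primary outcome only. The check is therefore a reading of the rules side by side, then an illustration on assumed values.

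**Rules side by side**

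| State at visit | Qmax | Voided volume | Residual urine |
|---|---|---|---|
| Indwelling catheter | set to 0 | no rule | no rule |
| Intermittent, cannot void | no rule | no rule | no rule |
| Intermittent, can void | measured | measured | measured |

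The first two rows are catheter states that the protocol foresees at entry and after the procedure. Five of their six cells have no rule. An unmeasured value in such a cell is deleted under {20c}. For residual urine, a site might instead enter an ultrasound reading from a drained bladder.

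**Illustration (all inputs assumed; none is in the documents)**

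Voiding men in both arms have Qmax m = 12 mL/s and residual m = 80 mL. A share c of each arm is catheterised at the visit, with the higher share placed in the PAE arm arbitrarily. If catheterised men receive the value v, the arm mean is (1 − c)·m + c·v. The PAE − TUMT difference is then (c_PAE − c_TUMT)·(v − m). If they are deleted, the difference is 0.

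Indwelling catheter, 5% TUMT v 10% PAE:
- Qmax, rule v = 0: 0.05 × (0 − 12) = −0.6 mL/s (PAE worse).
- Residual deleted: 0 mL.
- Residual entered as 0 mL: 0.05 × (0 − 80) = −4 mL (PAE appears better).
- Residual set at 300 or 500 mL: 0.05 × 220 = +11 mL or 0.05 × 420 = +21 mL (PAE worse).

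Indwelling catheter, 5% v 15%: Qmax −1.2 mL/s; residual 0 mL if deleted, −8 mL if entered as 0, +22 or +42 mL at 300 or 500 mL.

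Intermittent catheterisation without voiding, 2% v 10%: Qmax difference 0 if deleted; 0.08 × (0 − 12) = −0.96 mL/s if set to zero.

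Equal shares in both arms: every difference is 0.

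**Qmax-adjusted analysis {20b}**

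This uses a baseline value, so deletion here reflects severity before treatment, not treatment failure. The cost is narrower scope and lower precision. If 5% to 15% of 200 men were on intermittent catheterisation and could not void (assumed), 10 to 30 men would leave. The interval would widen by 1/√(1 − c) = 1.026 to 1.085, about 3% to 8%.

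**The case against.** The strongest reply is that coding of catheterised men is ordinary codebook or SAP content. Data management {19} describes a codebook explaining how each variable is to be entered, and an article need not repeat it. That would answer a mere omission. Here, however, the article states a partial scoring rule and a general deletion rule, and following both as written gives the selective loss described above. The unseen documents may close the gap, but the text as published does not.

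Other objections stand and limit the point:

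- A reader might infer that catheterised failures are scored with the best residual and that the comparison changes sign. The protocol assigns them no residual. The outcome is defined after voiding, so a missing value is at least as natural a reading, and a site could also measure at a voiding trial. With deletion, the illustration shows no reversal.
- A reader might infer that failures are hidden. They are not: catheterisation, of both types, is a separate secondary outcome, and Table 1 records catheter use at the same visits as uroflowmetry.
- A reader might infer that the Qmax-adjusted analysis loses the most obstructed men in general. Men with an indwelling catheter stay in with Qmax zero; only non-voiding men on intermittent catheterisation are lost.
- Some men who self-catheterise can void, so a blanket zero for that group would be wrong.
- Section {20a} allows medians, which a few catheterised men would move little.

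**Conclusion.** The point holds in limited form. The uroflowmetry rule is incomplete for outcomes and catheter states that the protocol itself foresees. Combined with deletion under an assumption of missing completely at random, it makes inclusion in the follow-up means depend on treatment success. The primary analysis, adjusted only for site and baseline IPSS, is untouched. The bias between arms requires unequal catheter use. Its size cannot be estimated, because the documents give neither catheter shares nor the spread of residual urine; the figures above show direction and mechanism only. It is worth correcting before analysis, because how catheterised men are handled can move the residual-urine comparison either way, and that choice should not be made with the data in view.

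**What to change.** State one scoring rule for all three measures and both catheter types:

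- For a man with an indwelling catheter, or on intermittent catheterisation and unable to void, Qmax and voided volume are set to zero at baseline and at every visit. Measured values are used for men on intermittent catheterisation who can void.
- A residual taken with a draining catheter is neither entered as 0 mL nor treated as missing completely at random. Residual urine is reported in voiding men, beside the proportion catheterised in each arm at that visit.
- A sensitivity comparison of residual urine ranks catheterised men as worst, using a rank-based test.

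A yes/no residual endpoint is optional. It loses resolution, and the only candidate limit in the protocol, 150 mL, is given as a general guide to catheter removal and not as an outcome threshold.

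The cost is wording in the outcome definition and the analysis plan. Catheter use is already collected at the same visits; at most, the form needs a field for whether a man on intermittent catheterisation could void. The change concerns outcome scoring only and leaves catheter care as it is.

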## Objectives {7}

The primary objective of this trial is to investigate the non-inferiority of PAE to TUMT in reducing LUTS 6 months post-procedure. The secondary objective is to compare LUTS (IPSS), patient satisfaction with the treatment, QoL (International Prostate Symptom Score—Quality of Life (IPSS-QoL), EQ-5D-5L and BPH Impact Index (BII)), health economics (EQ-5D-5L), erectile function (International Index of Erectile Function—Erectile Function (IIEF-EF)), ejaculatory function (Danish Prostatic Symptom Score—sexual questions (DAN-PSS-1-sex)), incontinence (International Consultation on Incontinence Questionnaire—Urinary Incontinence Short Form (ICIQ-UI-SF)), uroflowmetry outcomes, post-procedure duration of catheterisation, prostate volume (PV), prostate-specific antigen (PSA) and creatinine, incidence of side effects, de novo use of pharmacological LUTS treatment, and surgical re-treatment rates of TUMT and PAE during the 5 years following the procedures. The objective of this comparison is to create a reference for clinicians in patient counselling when choosing a MIST for the treatment of BPH.

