#### Arm 1: TUMT

TUMT is performed by a urologist and/or a trained urological nurse. In TUMT, a specially designed instrument that sends out microwave energy is inserted inside the prostate through the urethra. Cooling fluid circulates the instrument to prevent heat from damaging the wall of the urethra. To prevent the temperature from getting too high outside the prostate, a temperature sensor is positioned around the penis and inside the rectum. If the temperature reaches the safety limit, the microwave generator’s output will shut off automatically. Utilising the ProstaLund CoreTherm Device (ProstaLund, Lund, Sweden) microwave delivered by ProstaLund Feedback Treatment is used to heat the prostate at a range of 50–60 °C, destroying hyperplastic prostate tissue. As the prostate heals, it will shrink, reducing the blockage of urine flow and the symptoms of BHP. After the treatment, a transurethral catheter is inserted. This will be removed at the physician’s discretion when spontaneous voiding is achieved with an acceptable residual volume (generally < 150 mL), typically within 4 weeks.

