#### Arm 2: PAE

In PAE, an interventional radiologist will insert a small catheter into the vessels that supply blood to the prostate. Habitually arterial access is reached by a unilateral femoral sheath placed in the right common femoral artery under local anaesthesia. Digital subtraction angiography of the pelvic arteries is performed to assess the origin points of the internal iliac arteries and to map the vessels feeding the prostate. Pelvic arterial anatomy is complex and prostatic arteries exhibit a noticeable variation of origin, are often duplicated, and provide collaterals to the opposite half of the prostate and nearby structures. In addition, they are often markedly tortuous, making catheter advancement difficult. Cone beam computed tomography can be applied to assure correct placement or prevent non-target embolisation. Tiny embolisation particles are injected through the catheter and into the blood vessels to reduce the blood supply to the prostate. This procedure is intended at both sides of the prostate. Following the procedure, the prostate will shrink reducing the symptoms of BPH. A transurethral catheter is inserted before the procedure. In patients without a permanent catheter before PAE, this will be removed after the procedure. Patients with a permanent catheter before PAE will keep the catheter until spontaneous voiding is achieved with an acceptable residual volume (generally < 150 mL), typically within 4 weeks.

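### Catheter duration is defined only for men with a catheter placed after the procedure, so as written the between-arm comparison is of arm-dependent subsets

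*Protocol article*

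**What the plan says.** Objectives {7} of the protocol article includes "post-procedure duration of catheterisation" in the list of outcomes on which TUMT and PAE are to be compared, with patient counselling as the purpose.

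Outcomes {12} gives the counting rule: "If an indwelling catheter is placed after the procedure, the post-procedure duration of catheterisation will be defined as days from the procedure", running to the end of that catheter. It gives no value for a man who has no such catheter. The same item also covers catheter placement events, intermittent catheterisation, and catheterisation for other reasons during follow-up. Table 1 records catheter use at 3 and 6 months and at 1 and 2 years.

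The arms differ in how a catheter is used:

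- TUMT: "After the treatment, a transurethral catheter is inserted".
- PAE: "A transurethral catheter is inserted before the procedure". Then: "In patients without a permanent catheter before PAE, this will be removed after the procedure". And: "Patients with a permanent catheter before PAE will keep the catheter until spontaneous voiding is achieved".

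The trial admits both kinds of men. Eligibility can rest on "Severe urinary symptoms on IPSS (IPSS ≥ 20), an indwelling catheter, or intermittent catheterisation". The share catheterised at baseline is not given.

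Section {20c} states an intention-to-treat analysis, with pairwise deletion of missing data.

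**The concern.** Whether a man has a defined duration depends on something that happens after randomisation and is largely fixed by the arm he was allocated to. If the rule is followed as written, nearly the whole TUMT arm is set against a small PAE group selected for catheter dependence or for a problem after the procedure. Randomisation does not protect that comparison, and it does not fit the stated intention-to-treat principle.

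The rule also needs an end date. A man in either arm whose catheter is never removed has the worst result on this measure, yet no number.

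Time with a catheter is a practical difference between the two procedures that a patient would want to know. A figure drawn from unlike subsets could mislead the counselling that it is meant to support.

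**Working it through.** The plan gives no figure for this outcome (no expected days and no share of men with a catheter), so there is nothing of its own to reproduce. The check is a reading of the sections together, followed by an illustration on assumed values.

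**Step 1. Who meets the condition**

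| Group | Catheter by the arm description | Duration under the Outcomes {12} rule |
|---|---|---|
| TUMT, all treated men | inserted after treatment | yes |
| PAE, no permanent catheter | inserted before, removed after | none, unless re-catheterised |
| PAE, permanent catheter | existing one kept | literally none, as it was not placed afterwards; yes on a generous reading |

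Per 100 men treated in each arm, about 100 TUMT men have a value. In PAE it is at most the share with a permanent catheter, plus any re-catheterised.

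**Step 2. What happens to the rest.** No value is assigned. If a blank is treated as missing data, pairwise deletion removes it. The protocol does set values elsewhere when a catheter makes a measure unobtainable: baseline IPSS becomes 35 and Qmax becomes zero. It does not do so here.

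**Step 3. Possible effect, on assumed inputs.** Let q be the share with a catheter at baseline, a the mean TUMT days in men without one, and b the mean days in men with one, taken as equal in both arms. Use the generous reading, with no re-catheterisation in PAE and 0 days for PAE men with no catheter left.

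- TUMT mean = a(1 − q) + bq
- PAE mean among men with a duration = b
- PAE mean among all men = bq
- PAE minus TUMT, men with a duration = (b − a)(1 − q)
- PAE minus TUMT, all men = −a(1 − q)

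For a = 14, b = 21, q = 0.1, the TUMT mean is 14 × 0.9 + 21 × 0.1 = 14.7 days. The difference among men with a duration is 21 − 14.7 = +6.3. Among all men it is 2.1 − 14.7 = −12.6.

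| a / b (days) | q | TUMT mean | PAE − TUMT, men with a duration | PAE − TUMT, all men |
|---|---|---|---|---|
| 14 / 21 | 0.1 | 14.7 | +6.3 | −12.6 |
| 14 / 21 | 0.5 | 17.5 | +3.5 | −7.0 |
| 14 / 14 | 0.1 | 14.0 | 0 | −12.6 |
| 14 / 14 | 0.5 | 14.0 | 0 | −7.0 |
| 7 / 28 | 0.1 | 9.1 | +18.9 | −6.3 |
| 7 / 28 | 0.5 | 17.5 | +10.5 | −3.5 |
| 21 / 28 | 0.1 | 21.7 | +6.3 | −18.9 |
| 21 / 28 | 0.5 | 24.5 | +3.5 | −10.5 |

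The gap between the last two columns is b(1 − q), always in TUMT's favour under this set-up. The sign reverses when b exceeds a; when b equals a, the difference disappears. None of these inputs comes from the documents, which say only that catheters are typically out within four weeks.

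**The case against.** The strongest reply is that the sentence is a counting rule, not an analysis population. It says how to count days when there is a catheter, and 0 days otherwise is a natural reading. Having no catheter is a known state rather than missing data, so pairwise deletion need not apply. An analysis plan that is not shown could say all this.

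Part of that stands. The text does not expressly exclude men without a catheter, and their deletion is an inference. But an analysis plan that assigned 0 days would be supplying a rule that the written definition lacks. It would also still have to settle permanent catheters in PAE, which the literal wording leaves out.

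A reader might go further and infer that a t-test of all TUMT men against the worst PAE men is planned. The documents do not say so. Section {20a} names t-tests, chi-square tests and mixed models for secondary outcomes in general, chosen by data type and distribution, and assigns none of them to catheter duration.

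A reader might also infer that any PAE advantage is hidden or that permanent failures are lost from the trial. That is not supported either. Placement events, later catheterisation and catheter use at visits are collected, and acute urinary retention is a separate outcome. The proportion catheterised in each arm can be reported beside the duration.

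**Conclusion.** The point holds for the duration measure alone. As written, the definition covers essentially all TUMT men and only a selected minority or subset of PAE men, so the comparison announced in the Objectives would not be between the randomised groups. Men who are never free of the catheter have no end date. This follows from the outcome definition and the two arm descriptions, without any assumed number.

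The size cannot be derived from the documents. The illustration shows only that the difference could shrink to nothing or reverse. It rests on assumed days, an assumed baseline catheter share of 10% to 50%, equal days in both arms for men with a baseline catheter, and PAE men with existing catheters being counted. It is not a forecast.

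The primary outcome, the sample size and the non-inferiority conclusion are untouched. The definition should be corrected, but it does not threaten the trial's main result.

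**What to change.** Define the outcome for every randomised man as days from the procedure until he is free of an indwelling catheter:

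- 0 days if no indwelling catheter remains after the procedure;
- a catheter already in place beforehand is counted from the day of the procedure;
- a man still catheterised is censored at his last follow-up.

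Compare all randomised men, for example with Kaplan-Meier curves or with mean catheter days inside a fixed window such as up to the 3-month visit, preferably taking account of baseline catheter status. Cox regression is a poor default, because many PAE men would be catheter-free at day 0. Report duration among catheterised men as description only, beside the proportion catheterised in each arm.

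The cost is revised wording and minor analysis work. Catheter duration and use are already to be recorded, and nothing changes in how catheters are managed.

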
In Table 1, the specific time points for collection of secondary outcomes can be appreciated.

**Table 1 Tab1:** Time schedule

Visit	Screening	Intervention	FU 1	FU 2	FU 3	FU 4	FU 5	FU 6
Day	− 365 to − 2	0	1 month (± 5 days)	3 months (± 14 days)	6 months (± 14 days)	1 year (± 14 days)	2 years (± 14 days)	5 years (± 14 days)

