##### Follow-up management

Patients will be followed for 5 years post-procedure, with a total of four follow-up visits to the outpatient clinic at 3, 6, 12, and 24 months. The results from the long-term follow-up at 5 years will be completed with digital PROMs and assessment of the patient’s health record. Outcome data will be collected in accordance with Table 1. To complete the procedures and PROMs for the follow-ups at 3 months to 5 years, a 28-day window will be allowed, defined as 14 days before and 14 days after the due date. For the 1-month follow-up, the permitted window will be 10 days, 5 days before and 5 days after the due date.

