##### Iodinated contrast media

An iodinated contrast media, iodixanol (Visipaque® 270 mg/mL), is used during embolisation. Iodixanol is a dimeric, isosmolar, nonionic, water-soluble, iodinated X-ray contrast agent for intravascular administration. The most common side effect is minimal discomfort at the injection site (< 30%). Side effects associated with iodixanol are usually mild to moderate and of transient character. Serious side effects and deaths are extremely rarely seen and may include acute-on-chronic renal failure, acute renal failure, anaphylactic or anaphylactoid shock, allergic acute coronary syndrome (Kounis syndrome), cardiac or cardiopulmonary arrest, and myocardial infarction. Cardiac responses may be enhanced by an underlying disease or the study itself. Fatal cases of lactic acidosis have been described when iodinated X-ray contrast agents are given to patients in metformin therapy with elevated serum creatinine; local guidelines will be followed in such cases. Hypersensitivity reactions may occur as respiratory or cutaneous symptoms such as respiratory distress, rash, erythema, hives, pruritus, severe or toxic skin reactions, angioedema, hypotension, fever, laryngeal oedema, bronchospasm, or pulmonary oedema. Cases of vasculitis and Stevens-Johnson-like syndrome have been seen in patients with autoimmune diseases. Serious hypersensitivity reactions and anaphylactoid reaction/shock are rare (0.1–1%) [47]. Side effects can occur either immediately after injection or up to a few days later. Hypersensitivity reactions may occur independently of dose and mode of administration, and mild symptoms may be the first signs of a severe anaphylactic reaction/shock. In such cases, administration of the contrast agent will be discontinued promptly. A minor transient increase in serum creatinine is common after iodinated contrast agents but is usually of no clinical relevance.

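### Creatinine is said to help identify any kidney effect of the procedures, but the scheduled samples can show only lasting changes, and non-serious acute kidney injury is not a listed event

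*Protocol article*

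**What the plan says.** Under Outcomes {12}, creatinine is paired with PSA and given two roles. One concerns the disease: "A rise in serum creatinine can be a result of BPH with urinary retention". The other concerns the treatments: "Serum creatinine aids in the identification of any affection of the kidney from the procedures".

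In Table 1 the row "Blood test (PSA + creatinine" is marked at screening (day −365 to −2) and at follow-ups 2 to 5, which are 3 months, 6 months, 1 year and 2 years. It is not marked on the day of intervention or at 1 month. The Follow-up management section agrees, "with a total of four follow-up visits to the outpatient clinic at 3, 6, 12, and 24 months", so the first clinic visit after the procedure is the one at 3 months.

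The Iodinated contrast media section states that iodixanol is used during embolisation. On timing it says: "Side effects can occur either immediately after injection or up to a few days later". On creatinine it says: "A minor transient increase in serum creatinine is common after iodinated contrast agents but is usually of no clinical relevance". It also names acute and acute-on-chronic renal failure among serious effects that it describes as extremely rare.

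The Adverse events definition section restricts AE assessment to specific expected events between the procedure and 3 months and excludes spontaneous reporting. The SAEs section collects serious events over the same period on a dedicated form and uses inpatient register data for the cause of hospitalisation.

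**The concern.** A measure described as helping to find any kidney effect of the procedures should be taken when the effect that the protocol describes would be present. Here the described effect is early and short-lived, and the first sample comes about three months later.

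The gap is not symmetric. Procedural contrast belongs to PAE, and the description of TUMT mentions none. The screening CT angiography applies to both arms, so it does not account for this difference. Men with an eGFR of 35 mL/min or more may enter. The secondary outcomes are meant to inform patient counselling, so a reader of the results could take similar creatinine values at 3 months as evidence about the kidney in general, when they bear only on lasting change.

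**Working it through.** The protocol gives no numerical target for creatinine, so there is no figure to reproduce. The check compares the sampling times with the described timing of the effect, and then looks for other routes by which a renal event could enter the data.

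**1. Earliest post-procedure sample.** Table 1 sets follow-up 2 at "3 months (± 14 days". With 30.4 days per month:

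- nominal day: 3 × 30.4 = 91.2
- earliest: 91.2 − 14 = 77.2
- latest: 91.2 + 14 = 105.2

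The first sample is therefore at about day 77 to 105, and nothing is scheduled in the first 77 / 7 = 11 weeks.

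**2. Timing of the described effect.** The contrast section gives onset from immediately to a few days after injection and describes the rise as transient. It gives no duration. For a scheduled sample to register a contrast-related rise, the rise would have to persist for about 11 weeks at least. That it normally resolves sooner is an inference from the word transient, not a figure in the protocol.

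**3. Baseline.** The comparison value may be up to 365 days old on the day of the procedure. The interval between the two measurements bracketing the procedure can thus reach about 365 + 105 = 470 days.

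**4. Other routes into the data.**

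| Type of renal event | Route in the protocol as published |
|---|---|
| Persistent impairment | Creatinine at 3, 6, 12 and 24 months |
| Acute and serious (for example, needing admission) | SAE form and register data, 0–3 months; hospital admission is also a secondary outcome |
| Acute, not serious, noted in the health record | Not among the listed expected events |
| Acute, silent, never measured | None |

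For the third row, the 3-month incidence list in Outcomes {12} names urinary tract infection, acute urinary retention, dysuria, haematuria, post-embolisation syndrome, hospital admission and hospitalisation time. The lists in the Adverse events definition section add sexual side effects, access-site haematoma, pseudoaneurysm, non-target embolisation and vessel injury with bleeding. Neither place lists a renal event.

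**The case against.** The case for leaving the text alone has real force.

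- **The missed rise is mostly unimportant by the protocol's own account.** It is described as minor and usually of no clinical relevance, and renal failure as extremely rare. This stands, and it limits the weight of the point.
- **Creatinine is only said to aid identification.** The protocol never makes the transient contrast rise an outcome, and sampling at 3 to 24 months suits a question about lasting renal function. This also stands. What remains is that the stated purpose covers any effect of the procedures, which is wider than that question.
- **Important acute events are captured elsewhere.** A reader might infer that acute renal harm after PAE would go unseen. The documents do not support that: serious events and admissions over 0–3 months are recorded, unexpected SAEs go to the ethics committee, and SAEs resulting in organ failure are a ground for closing the study.
- **No statement of renal safety is planned.** A reader might infer that the trial will report PAE as free of kidney effects. No section says so. A null result at 3 to 24 months is informative about lasting impairment and would mislead only if read as covering acute injury.
- **Relief of obstruction might seem to mask harm.** The protocol links retention to raised creatinine, so a within-arm fall could hide a procedural effect. Between randomised arms a shared benefit cancels, and the two treatments are expected to perform similarly. Distortion would need a material difference in relief, which nothing in the protocol shows.
- **The full case report form is not shown.** The protocol says that AE definitions will be specified in REDCap, and a renal item may exist there. That is possible. However, the article itself confines AE assessment to the specific expected events that it lists, and no renal event is among them.

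**Conclusion.** The point holds in a limited form. The scheduled creatinine samples support a statement about persistent renal function from 3 to 24 months. They do not support the wider purpose of identifying any kidney effect of the procedures, because the first sample comes at about day 77 to 105 while the contrast effect is described as arising within days and passing. Serious acute events have a route into the data. A non-serious acute kidney injury, on the published text, does not.

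This rests on two assumptions: that transient means resolved before about 11 weeks, for which the protocol gives no duration, and that the published event lists match the data collection form. No size can be put on the missed rises, since the protocol gives neither their frequency nor their time course, and any decay calculation would only return its own assumptions.

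This is a minor secondary safety point and a cheap improvement. It does not touch the primary IPSS comparison, the sample size or the non-inferiority conclusion.

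**What to change.** Three changes:

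1. In Outcomes {12}, restate the creatinine outcome as persistent renal function, meaning the change from baseline at 3, 6, 12 and 24 months compared between arms. Drop the suggestion that it identifies any kidney effect of the procedures.
2. Add acute kidney injury or acute renal failure to the predefined 0–3 month events, in both arms and with one definition in REDCap, extracted from the health records that are already reviewed for adverse events.
3. State in the analysis and reporting text that the 3-month creatinine comparison does not exclude acute renal effects.

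The cost is outcome wording and one extra event field. No new sample or visit is needed. Because the source is the health record, the item can also be completed for men already treated. The downside is a narrower renal claim, and rises that nobody measured in routine care will still be unseen.
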